**III. Informed Consent and Participant Confidentiality**

Separate written informed consent will be obtained from participants each time we hold an interview with them (*i.e.* FGD, IDI, *etc.*). For screened-out participants the interviewer will ask for verbal informed consent before commencing the interview. The moderator of each interview will ensure confidentiality.

We will stress to all participants that they are free to decline participation in the qualitative study and that this will not in any way affect their participation in the main trial.

**IV. Staff training**

The Social Science Coordinator will train all interviewers who will be collecting data for the qualitative research component. The QRC training focuses on qualitative data collection methods such as IDIs and FGDs. During the training methods for selecting the participants, obtaining consent and general methods for conducting the interviews are discussed. Prepared interview guides are also discussed. These guides have been developed based on MIRA trial CRF questions, items used in previous studies, and newly created questions, appropriate for this work.

The staff training offers an opportunity for validation of these guides, and after training the guides will be pilot tested before used with study participants.

**V. Qualitative data analysis**

Qualitative data analysis is an iterative process that continues from the design stage to the reporting of research results. The Social Science Coordinator for MIRA will give site staff as much input as possible in the administration of the QRC protocol. We also recognise the fact that the researcher collecting the data plays a crucial role in the analysis of qualitative data. Ibis Reproductive Health will only play a coordinating and supporting role to the site staff. However, there is need for constant liaising between site staff, the individuals interested in a research topic from the MIRA group and Ibis in the analysis of data.

Research staff in MIRA will interview in the site language (*i.e.* isiZulu, Sesotho or Shona), tape record, transcribe and translate the interviews into English. They will then present these in a form ready for thematic analysis to interested scientists in the larger group. The data will be analysed using Atlas/ti, qualitative analysis software which will be made available to the site. The selection of Atlas was based on considerations such as availability of local expertise, backup for training and common research goals in the larger MIRA trial group. It will also enable us to use the constant comparison method which enables the comparison of themes by various categories of the data (e.g. Donovan et al, 2000; Pope et al, 2002). The thematic analysis will be conducted according to guidelines developed for the interviews and observations that will be uniform across sites to ensure that the same factors are studied in different settings.

It is also recommended that more than one person code and interpret the qualitative data. In each case there will be two social scientists that will code and interpret selected transcripts and compare their interpretations. However, if only one person interprets the data without the benefit of multiple coders, the person needs to be skilled and be an experienced researcher (Dingwall et al, 1998). The researcher should keep detailed records of the analysis process to show how one interprets the data and reaches conclusions. This will create an ‘audit trail’ and ensure that the data analysis is rigorous, and will enable multiple reviewers to conduct independent analyses and compare the findings (Dingwall et al, 1998; Ulin et al, 2002). Summaries of results will be presented by themes and main findings noted to be compared across sites.

**Background**

Herpes simplex virus is the commonest cause of genital ulcer globally 66-69. Both genital ulcers and HSV specifically have been associated with HIV transmission. From multiple studies, the presence of HSV is associated with a relative risk of HIV acquisition of 2.1 compared with HSV negative persons 70. Furthermore, it has been observed that persons with recent HSV infection appear to have an even greater elevation in the risk of HIV acquisition than persons with more remote HSV infection 71. It is therefore of interest to characterize the recency distribution of HSV infection in order to further understand the impact of recent and remote HSV infection on HIV acquisition.

In the context of the MIRA study, HSV infection will be determined by serologic reactivity in the Focus Elisa test 72. A recently published modification of the test procedure allows for reactive specimens to be further characterized in terms of the avidity of HSV antibodies 73. The immune response to infection with HSV and other pathogens is associated with increased avidity of antibodies over time 74-78. By correlating avidity index scores among persons with known timing of infection, the time course of avidity index has been modelled, and proposed cut-off scores have been tested 73.

**Objectives**

The specific objectives of the study are:

1. Determine the prevalence of recent HSV infection in a cohort of HIV uninfected women in Soweto as measured by avidity index score ≤40
2. Describe the distribution of avidity index scores for HSV seropositive women in Soweto
3. Describe the relationship between baseline serologic reactivity with the Focus HSV Elisa and avidity index

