In April 2005, the study statistician did a recalculation of the sample size based on actual HIV incidence rates to date. The overall annual incidence was found to be 3.5%. In order to maintain 90% power to detect a 33% reduction in HIV infection, it was estimated that 500 more women were needed in the trial, bringing the total sample size to 5000 women. Each site increased their target enrollments: Harare to 2500, Durban to 1500, and Johannesburg to 1000. In addition, re-calculations of the estimated number of infections and woman-years of data needed to detect a difference between study arms have produced higher figures. Thus while previous versions of the MIRA Technical protocol listed 280 incident infections needed, and 3500 woman-years of data per arm, we are now operating under the estimates of 293 incident cases and 4000 woman-years per arm.

The final enrollment numbers for the study sites were 2502 at UZ-UCSF, 1515 at MRC, and 1028 at PHRU. A total of 5045 women were enrolled in the study.

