**Research design**

This ancillary study is a pilot/feasibility laboratory study. We propose to use stored serum specimens from the baseline visit of participants enrolling in the MIRA trial at PHRU. Laboratory personnel will identify women who had a positive test for HSV-2 in the enrolment sample. Residual serum samples from these participants will be retrieved from storage. The available samples will be thawed and testing repeated in duplicate with the modified assay according to the published method 73. An avidity index value for the enrolment sample will be determined from the paired results, by dividing the treated OD value by the untreated OD value and multiplying by 100.

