**Study population**

Participants in this ancillary study will be women who have consented and enrolled in the MIRA study, who tested positive for HSV-2 in the enrolment sample, and who have stored aliquots of serum available at Contract Laboratory Services from the enrolment sample.

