**Analysis**

For the first study objective, assuming that 200, 300, or 550 samples were available for testing from the participants enrolled to date and found to be HSV seropositive, the confidence limits for the given prevalence were calculated by exact methods for binomial proportions (Table).

The second and third objectives would be presented with simple descriptive statistics.

|  | N = 550 | | N = 300 | | N = 200 | |
| --- | --- | --- | --- | --- | --- | --- |
| Prevalence | **LCL** | **UCL** | **LCL** | **UCL** | **LCL** | **UCL** |
| 0.50 | 0.4574 | 0.5426 | 0.4420 | 0.5580 | 0.4287 | 0.5713 |
| 0.10 | 0.0762 | 0.1282 | 0.0685 | 0.1397 | 0.0622 | 0.1502 |
| 0.05 | 0.0341 | 0.0727 | 0.0283 | 0.0811 | 0.0242 | 0.0900 |
| 0.01 | 0.0400 | 0.0236 | 0.0021 | 0.0289 | 0.0012 | 0.0357 |
| 0.005 | 0.0011 | 0.0159 | 0.0008 | 0.0239 | 0.0001 | 0.0275 |
| 0.001 | <0.0001 | 0.0101 | - | 0.0122٭ | - | 0.0183٭ |

LCL, lower confidence limit; UCL, upper confidence limit; ٭1-sided, 97.5% confidence bound

Development of the assay had validated a threshold avidity index value of 40 to define recent infection. The sensitivity and specificity of this rule for samples drawn within six weeks of initial onset of HSV-2 was 81% and 86%, respectively. As the likelihood of observing one such event in a cohort is unknown, but likely to be small, we propose to test 550 baseline specimens to optimize the chances of observing a recent seroconversion.

Data would be collected and entered in a separate database, with samples identified by study number. Data analysis would be undertaken by a PHRU statistician.

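### HSV-2 sub-study (Appendix 16.4): Objective 1 asks for the prevalence of recent infection in the HIV-uninfected cohort, but the planned analysis estimates the proportion recent among HSV-2 seropositive women only

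*Protocol*

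**What the plan says.** Appendix 16.4, Objectives, lists as its first aim "Determine the prevalence of recent HSV infection in a cohort of HIV uninfected women in Soweto as measured by avidity index score ≤40". The only restriction on the population is HIV-negative status. The second aim in the same list is narrower: "Describe the distribution of avidity index scores for HSV seropositive women in Soweto".

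The sections that follow work in the narrower population throughout:

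- Research design: "Laboratory personnel will identify women who had a positive test for HSV-2 in the enrolment sample", and residual serum is retrieved for those women.
- Study population: participants are consented MIRA enrolees "who tested positive for HSV-2 in the enrolment sample" who also have stored serum.
- Analysis: for the first objective, precision is worked out "assuming that 200, 300, or 550 samples were available for testing from the participants enrolled to date and found to be HSV seropositive", and "the confidence limits for the given prevalence were calculated by exact methods for binomial proportions". The section ends with the statement that "we propose to test 550 baseline specimens to optimize the chances of observing a recent seroconversion".

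Elsewhere in the protocol, section 7.1.1 gives site enrolment: "The final enrollment numbers for the study sites were 2502 at UZ-UCSF, 1515 at MRC, and 1028 at PHRU". PHRU is the Soweto site. Section 10.2 (Specimen Collection and Testing) has every woman tested for HSV-2 at enrolment, and allows for indeterminate as well as negative results.

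**The concern.** The first objective and its analysis refer to different populations. The objective asks what share of HIV-uninfected women in the cohort have a recent HSV-2 infection. The analysis yields the share of seropositive women whose infection is recent. A seronegative woman is a member of the objective's cohort and, by this serological measure, is not recently infected. She should count in the denominator with nothing in the numerator, but the plan has no step that brings her in.

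The two quantities differ whenever any enrolled woman is seronegative, and always in the same direction: the planned figure is the larger. If it is reported under the wording of Objective 1, recent HSV-2 infection will look more common in the cohort than it is. The precision table would also be describing a different quantity from the one the objective names.

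**Working it through.** **1. Which denominator does the plan use?** The table can be reproduced. Take x = n × prevalence, rounded to a whole number with halves rounded up, and compute exact (Clopper-Pearson) 95% limits on n seropositive samples.

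- n = 550, prevalence 0.10: x = 55, limits 0.0762 to 0.1282, as printed.
- n = 550, prevalence 0.05: x = 28, limits 0.0341 to 0.0727, as printed.
- n = 300, prevalence 0.05: x = 15, limits 0.0283 to 0.0811, as printed.
- n = 200, prevalence 0.01: x = 2, limits 0.0012 to 0.0357, as printed.

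In all, 33 of the 34 numeric limits agree. The exception is the lower limit for n = 550 at prevalence 0.01. It is printed as 0.0400 but computes to 0.0040 (x = 6), and the printed value exceeds its own upper limit of 0.0236. That is a decimal slip unrelated to the present point. The reproduction confirms that the denominator for Objective 1 is the number of seropositive samples.

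**2. Relation between the two quantities.** Let s be HSV-2 seroprevalence among the site's enrolees and p the proportion recent among seropositives. With seronegative women counted as not recent,

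cohort prevalence = p × s,

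so p exceeds cohort prevalence by the factor 1/s.

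**3. Size of the factor.** The protocol states no value of s for the site, so these are assumptions:

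| Assumed s | Factor 1/s |
|---|---|
| 30% | 3.3 |
| 40% | 2.5 |
| 50% | 2.0 |
| 60% | 1.67 |
| 70% | 1.43 |
| 80% | 1.25 |

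A planned result of 10% among seropositives would thus mean a cohort prevalence between 0.10 × 0.30 = 3% and 0.10 × 0.80 = 8%.

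**4. One special case.** Suppose 550 were every seropositive woman among the 1,028 enrolled at PHRU. Then s = 550/1028 = 0.535 and the factor is 1028/550 = 1.87. On the target enrolment of 1,000 it would be 1000/550 = 1.82. Under that assumption, with exact 95% limits:

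| Recent cases | Over 550 seropositives | Over 1,028 enrolees |
|---|---|---|
| 55 | 10.0% (7.62 to 12.82) | 5.35% (4.06 to 6.91) |
| 28 | 5.09% (3.41 to 7.27) | 2.72% (1.82 to 3.91) |
| 6 | 1.09% (0.40 to 2.36) | 0.58% (0.21 to 1.27) |

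**The case against.** The best defence is that this is loose wording in an otherwise open design. Avidity can be measured only on reactive sera, and Objective 1 is qualified by the avidity cut-off. The appendix's background section says the aim is to describe how infections divide into recent and remote, which is a split among infected women. On that reading the HIV-uninfected cohort is merely the source of the samples. The eligibility and analysis text states the seropositive restriction plainly, so a careful reader is not misled.

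Much of this stands. It makes rewording the objective a legitimate remedy, and it keeps the point small. It does not remove the mismatch. That only reactive sera can be assayed settles who is assayed, not who belongs in the denominator. The authors also wrote the seropositive restriction into Objective 2 and left it out of Objective 1, so the text does not support treating the two populations as the same.

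Two stronger readings are tempting and should be set aside:

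- A reader might infer from 550 and 1,028 that the estimate is nearly twice too high. The protocol does not support that as a fact. The 550 is one of three assumed counts of available samples at an interim date, while 1,028 is final enrolment. Seropositive women without stored serum are excluded from the count, so the true seropositive number could be higher and the factor smaller. It could also be lower and the factor larger.
- A reader might infer that the error carries into an attributable-risk estimate for HIV. The appendix plans no such analysis. It describes a pilot laboratory study, with simple descriptive statistics for its other two objectives.

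The absolute difference may also be small. The Analysis section expects recent infections to be rare. In the 6-case row above the gap is about half a percentage point and the intervals overlap.

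**Conclusion.** The point holds as a mismatch between Objective 1 and its analysis. As written, the plan delivers the proportion recent among HSV-2 seropositive women and not the cohort prevalence that the objective names. Read as the latter, the estimate is too high by 1/seroprevalence. The direction is certain if any enrolee is seronegative. The size is not known from the documents, and the 30% to 80% range is a reviewer's assumption. The calculation takes seronegative women as not recently infected by this measure, and tested seropositives as representative of all seropositives at the site. The matter is confined to a pilot sub-study and does not touch the main trial's HIV endpoint. It is still worth correcting because the data needed are already collected.

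**What to change.** Choose one of two routes and make the Objectives, Study population and Analysis sections of Appendix 16.4 agree.

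**Keep Objective 1 as worded.** Estimate (recent / seropositives tested) × (seropositives / all PHRU enrolees with a definite enrolment HSV-2 result), with a confidence interval that reflects uncertainty in both factors. The first factor allows for seropositive women without stored serum, provided those tested are representative. If every seropositive woman is tested and every enrolee has a definite result, the product reduces to recent cases over all enrolees and an exact binomial interval suffices. Add a sensitivity analysis that counts indeterminate enrolment results first as negative and then as positive. Recompute the precision table for this quantity over a stated range of seroprevalence. Report the recent fraction among seropositives separately, labelled as such.

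**Or restate Objective 1** as the proportion of HSV-2 seropositive women at the site whose infection is recent by the avidity cut-off. The table's denominator then stands.

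Either route should also correct the misprinted lower limit for n = 550 at prevalence 0.01. The cost is a wording change or a recomputed table plus a rule for indeterminate results. No new specimens or assays are needed, because HSV-2 testing at enrolment already covers all women.

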**Research design**

This ancillary study is a pilot/feasibility laboratory study. We propose to use stored serum specimens from the baseline visit of participants enrolling in the MIRA trial at PHRU. Laboratory personnel will identify women who had a positive test for HSV-2 in the enrolment sample. Residual serum samples from these participants will be retrieved from storage. The available samples will be thawed and testing repeated in duplicate with the modified assay according to the published method 73. An avidity index value for the enrolment sample will be determined from the paired results, by dividing the treated OD value by the untreated OD value and multiplying by 100.

**Study population**

Participants in this ancillary study will be women who have consented and enrolled in the MIRA study, who tested positive for HSV-2 in the enrolment sample, and who have stored aliquots of serum available at Contract Laboratory Services from the enrolment sample.

**Analysis**

For the first study objective, assuming that 200, 300, or 550 samples were available for testing from the participants enrolled to date and found to be HSV seropositive, the confidence limits for the given prevalence were calculated by exact methods for binomial proportions (Table).

The second and third objectives would be presented with simple descriptive statistics.

|  | N = 550 | | N = 300 | | N = 200 | |
| --- | --- | --- | --- | --- | --- | --- |
| Prevalence | **LCL** | **UCL** | **LCL** | **UCL** | **LCL** | **UCL** |
| 0.50 | 0.4574 | 0.5426 | 0.4420 | 0.5580 | 0.4287 | 0.5713 |
| 0.10 | 0.0762 | 0.1282 | 0.0685 | 0.1397 | 0.0622 | 0.1502 |
| 0.05 | 0.0341 | 0.0727 | 0.0283 | 0.0811 | 0.0242 | 0.0900 |
| 0.01 | 0.0400 | 0.0236 | 0.0021 | 0.0289 | 0.0012 | 0.0357 |
| 0.005 | 0.0011 | 0.0159 | 0.0008 | 0.0239 | 0.0001 | 0.0275 |
| 0.001 | <0.0001 | 0.0101 | - | 0.0122٭ | - | 0.0183٭ |

LCL, lower confidence limit; UCL, upper confidence limit; ٭1-sided, 97.5% confidence bound

Development of the assay had validated a threshold avidity index value of 40 to define recent infection. The sensitivity and specificity of this rule for samples drawn within six weeks of initial onset of HSV-2 was 81% and 86%, respectively. As the likelihood of observing one such event in a cohort is unknown, but likely to be small, we propose to test 550 baseline specimens to optimize the chances of observing a recent seroconversion.

Data would be collected and entered in a separate database, with samples identified by study number. Data analysis would be undertaken by a PHRU statistician.

**Ethical considerations**

All volunteers are requested to provide consent for storage of specimens at enrolment. The research proposed in this ancillary study would be covered by the language contained in the storage consent document. No additional approval would be required from the local Institutional Review Board for this research. However, the IRB would need to be informed of the proposed research.

***Introduction to the Standard of Care (SOC)***

The investigators of the Methods for Improving Reproductive Health in Africa (MIRA) trial have established a Standard of Care (SOC) package for HIV-positive women who seroconvert during their participation in a randomized, clinical trial to determine whether the diaphragm with Replens gel prevents HIV acquisition in women. The provision of such a care package for MIRA research participants comes in response to a policy proposal by the Gates Foundation and a need to address the ethical challenges presented by HIV prevention trials for which clear guidelines do not exist.

Currently, the governments of Zimbabwe and South Africa are implementing programs for the distribution of antiretroviral (ARV) therapy as well as other care services for people living with HIV/AIDS (PLWHA). Recently, antiretroviral drugs have become more affordable and therefore more accessible to African countries that previously had very limited access. Because antiretroviral treatment can greatly affect the quality of life and longevity of people living with HIV/ AIDS (PLWHA), it is critical to deliver it to those in need. Despite efforts by the governments of Zimbabwe and South Africa to deliver treatment, each country is faced by challenges that translate into original treatment targets not being fully met. As these government programs improve their systems to deliver ARVs and other related services, clinical trials such as MIRA have an opportunity to fill in the gaps of HIV-related services and care when government resources fall short.

The investigators of the MIRA trial propose a four-component policy of care and treatment to participants who are identified as HIV-positive during the trial. The four main components include 1) Psychosocial support and counseling, 2) Monitoring of disease progression using CD4 counts, 3) Screening for opportunistic infections, and 4) Access to ARV therapy.

Women who are HIV negative at screening, enroll into the study and are then found to be positive at subsequent follow-up visits (seroconverters) will be offered these services on an on-going basis throughout the life of the trial, currently scheduled to end in May 2007. Care and services at each of the three MIRA sites (Harare, Zimbabwe; Durban, South Africa; Johannesburg, South Africa) may vary, depending on the availability of outside resources in each area. To ensure the quality of care and distribution of services and treatment, systems of monitoring and evaluation will be implemented at each site.

***Goals***

The two goals of the Standard of Care (SOC) component of the MIRA trial are:

- To inform and educate women who seroconvert during their participation in the MIRA trial about available local services that may monitor their health, HIV infection, and emotional wellbeing.
- To encourage and assist these women to access these services during their participation with MIRA, which will in turn help to ensure a sustained relationship with these providers when the MIRA trial ends.

